#### Primary outcome

It has been suggested that the ability to perceive and process internal bodily signals comprises different dimensions of both subjective and objective interoceptive sensitivity [65]. Therefore, both a self-report measure and two objective measures are used to assess interoceptive sensitivity as the study’s primary outcome. To objectively quantify individual differences in behavioral interoceptive performance, also referred to as interoceptive accuracy (IA) [65], objective measures of both cardiac and gastric interoceptive ability will be assessed.

#### Interoceptive sensitivity

As part of the online questionnaires, participants’ subjective beliefs (self-report) in their interoceptive ability will be assessed with the German version [66] of the Multidimensional Assessment of Interoceptive Awareness (MAIA [57];). The 32-item multidimensional instrument assesses different aspects of interoceptive body awareness with eight subscales (*Noticing, Non-Distracting, Not-Worrying, Attention regulation, Emotional awareness, Self-Regulation, Body listening, Trust*). Each item (e.g., “I am able to consciously focus on my body as a whole.”) is rated on a 6-point Likert scale ranging from *never* (= 0) to *always* (= 5). Previous research has supported the scale’s validity and internal consistency, with Cronbach’s α ranging between .56 and .89 for the different subscales [66].

#### Cardiac interoceptive accuracy

Cardiac interoceptive accuracy is measured using the well-established Heart Beat Perception Task (HBPT [55];). During this task, participants are positioned on an adjustable examination couch and asked to sit in a comfortable, semi-upright position. They are instructed to listen to and silently count their own heartbeats (intervals of 25, 35, 45, and 100 seconds, respectively) without using any additional aid (e.g., taking their pulse manually). Participants are not aware of the lengths of the intervals, and their order of presentation is counterbalanced across participants. Simultaneously, an electrocardiogram (ECG) of the objective heartbeats is recorded using a heart rate variability (HRV) scanner from BioSign GmbH, with clamp electrodes placed at both wrists (sampling rate of 500 Hz, 16-bit resolution). An IA score is calculated using the following commonly used formula:$$\textrm{IA}\ \textrm{score}=\frac{1}{4}\sum \Big(1-\frac{\left(\left|\textrm{recorded}\ \textrm{heartbeats}-\textrm{counted}\ \textrm{heartbeats}\right|\right)}{\textrm{recorded}\ \textrm{heartbeats}}$$

IA scores range between 0 and 1, with higher scores indicating a smaller difference between recorded and reported heartbeats, i.e., a higher interoceptive accuracy.

#### Gastric interoceptive accuracy

As a domain-specific measure of interoceptive accuracy, gastric interoception is measured using the two-step Water Load Test (WLT-II [64];). Following the procedure by van Dyck and colleagues [64], participants are instructed to drink still water at room temperature over two successive 5-minute intervals. During the first phase, participants are asked to drink water until reaching the point of perceived satiation. The first phase is followed by a second one, where participants are instructed to drink water until reaching the point of maximum stomach fullness. Participants are not informed that there will be a second drinking phase to rule out any influence on the amount of water consumed during the first phase. Participants are instructed to drink the water through long straws from non-transparent 5-l flasks that are filled with 1.5 l of water. Participants receive a refilled flask for each drinking phase. After giving the instructions, study assistants leave the room during each phase. After each phase, the amount of water consumed (in milliliters) is recorded in another room. Participants are instructed to refrain from eating and drinking at least 2 hours before the session and are encouraged to use the toilet before being tested.

Different WLT-II scores can be calculated. In addition to the amount of water consumed up to satiation (step 1: water volume required to produce satiation [sat_ml]) and maximum fullness (step 2: additional water volume required to produce maximum fullness [Δfull_ml]) and the total water volume (total_ml), an individual index of gastric interoception (sat_%) will be calculated. It is defined as the percentage of satiation to maximum fullness and it is not confounded with stomach capacity. It is calculated using the following formula [64]: $$\textrm{sat}\_\%=\frac{\textrm{sat}\_\textrm{ml}}{\textrm{total}\_\textrm{ml}}\ \textrm{x}\ 100.$$

In addition, subjective sensations related to the WLT-II are assessed using the WLT-II questionnaire [64]. Before and after each drinking phase, participants are asked to complete 8 items, rating their momentary feelings of satiation and fullness as well as sensations of discomfort, guilt, sluggishness, nausea, and arousal. Items are rated on a 7-point Likert scale that ranges from *no sensation/not at all* (= 1) to *extremely* (= 7). According to van Dyck and colleagues [64], the WLT-II shows satisfactory repeatability over time for both drinking periods and proves to be a reliable and valid instrument for assessing gastric interoception.

### Secondary outcomes

#### Intuitive eating

Intuitive eating is measured with the German version [9] of the Intuitive Eating Scale-2 (IES-2 [4];). The scale assesses the four aspects of intuitive eating: *Unconditional permission to eat* (UPE, 6 items, e.g., “If I am craving a certain food, I allow myself to have it.”), *Eating for physical rather than emotional reasons* (EPR, 8 items, e.g., “I find other ways to cope with stress and anxiety than by eating.”), *Reliance on hunger and satiety cues* (RHSC, 6 items, e.g., “I rely on my hunger signals to tell me when to eat.”), and *Body-food choice congruence* (B-FCC, 3 items, e.g., “I mostly eat foods that give my body energy and stamina.”). All 23 items are rated on a 5-point Likert scale ranging from *strongly disagree* (= 1) to *strongly agree* (= 5). Therefore, higher mean values reflect higher levels of intuitive eating. Previous research has supported the scale’s validity as well as its internal consistency for the total score (Cronbach’s α = .89) and each of the four subscales, with Cronbach’s α ranging from .73 to .91 [9].

#### Maladaptive eating

Ratings of maladaptive eating are obtained from the German version [67] of the Dutch Eating Behavior Questionnaire (DEBQ [53];), a widely used measure of eating styles. Responses to its 30 items are rated on a 5-point Likert scale that ranges from *never* (= 1) to *very often* (= 5). Three subscales reflect the different eating styles of restraint eating (10 items, e.g., “I deliberately eat less in order not to become heavier.”), emotional eating (10 items, e.g., “I have the desire to eat when I am feeling lonely.”), and external eating (10 items, e.g., “I eat more than usually when I see others eating.”). Previous research [53, 67] has supported the scale’s validity and the subscales’ reliability, with Cronbach’s α of the three subscales ranging between α = .87 and .95.

To be able to not only measure emotional eating as a coping strategy to deal with negative emotions as in the DEBQ, but also to assess emotional eating related to negative as well as positive emotions, the Salzburg Emotional Eating Scale (SEES [60];) was used. The SEES allows for a differentiation between four types of emotions (Happiness, sadness, anger, anxiety) and between increased or decreased food intake in response to emotions. It consists of 20 items that each begin with the stem “When I feel/am …” , followed by an adjective describing an emotion. Response categories range from 1 (*I eat much less than usual*) to 5 (*I eat much more than usual*). Internal consistency of the four subscales ranges between Cronbach’s α = .71 and .87 in different samples [60].

#### Maladaptive and pathological eating

Disordered eating behavior is assessed using the German version [68] of the SCOFF [59]. The 5 items (e.g., “Do you believe yourself to be fat when others say you are too thin?”) are rated on a dichotomized scale (*yes* or *no*), with a total score of ≥ 2 as a cutoff point to select persons at risk of developing an eating disorder. In a validation study, Cronbach’s α was .66 [68].

Loss of control over eating is measured using a German translation of the Brief Loss of Control Over Eating Scale (LOCES-B [69];). The original 7 items (e.g., “I continued to eat past the point when I wanted to stop.”) were translated into German by two independent psychologists and then back-translated, following the WHO guidelines [70]. On a 5-point Likert scale ranging from *never* (=1) to *always* (=5), participants rate how often they experienced loss of control during the past 28 days. The scale’s internal consistency reached Cronbach’s α = .93 in the original validation study [69].

Binge eating is measured with the following two items of the German version [54] of the Eating Disorder Examination-Questionnaire (EDE-Q [71];): (a) “Over the past 28 days, how many times have you eaten what other people would regard as an unusually large amount of food (given the circumstances)?” and (b) “On how many of these times did you have a sense of having lost control over your eating (at the time you were eating)?”. Participants are asked to rate the frequency of binge eating in terms of number of episodes in the past 28 days, with higher scores reflecting higher levels of binge eating.

### Additional and control variables

#### Self-efficacy in using physiological signals of hunger

Self-efficacy in using physiological signals of hunger is assessed using a German translation of the eponymous subscale of the Multidimensional Internally Regulated Eating Scale (MIRES [58];). Following the WHO guidelines [70], the original items were translated into German by two independent psychologists and then back-translated. Its 6 items (e.g., “I find it easy to let my hunger determine when I eat.”) are rated on a 7-point Likert scale, ranging from 1 (*completely untrue for me*) to 7 (*completely true for me*). In the original validation study, the composite reliability was .90 [58].

#### Individual and familial eating habits

Individual eating habits and routines during mealtime are assessed using 9 items [72]. The items (e.g., “I chew my food thoroughly.”) are rated on a 5-point Likert scale that ranges from *never* (= 1) to *always* (= 5). Familial eating habits and eating traditions [42] are measured with 15 items (e.g., “Food is very important to our family.”) that are rated on a 5-point Likert scale ranging from *strongly disagree* (= 1) to *strongly agree* (= 5). In a preliminary study [9], internal consistency of this scale reached Cronbach’s α = .76.

#### Eating motives

Motives underlying eating behavior are measured using the following three subscales of the Eating Motivation Survey (TEMS [63];): (a) *Liking* (5 items; e.g., “I eat what I eat, because I think it’s delicious.”), (b) *Need and Hunger* (4 items, e.g., “I eat what I eat, because I’m hungry.”), and (c) *Pleasure* (5 items, e.g., “I eat what I eat, because I enjoy it.”). Items are rated on a 7-point Likert scale that ranges from *never* (= 1) to *always* (= 7). Previous research [63] has supported the scale’s validity and the subscales’ reliability, with Cronbach’s α = .84 (*Liking*), and .77 (*Pleasure*). The internal consistency of the *Need and Hunger* subscale was comparably low, with Cronbach’s α = .48 (*Need and Hunger*).

#### Readiness to change

Self-generated items are used to evaluate participants’ readiness to change towards a more mindful and intuitive approach to eating. Items were generated based on the *Transtheoretical Model* (TTM [73];) that conceptualizes behavior change as a process that involves progression through different stages of change (SOC). Readiness to change is assessed by four items (e.g., “When I eat, I consciously pay attention to my bodily signals (e.g., feelings of hunger or satiety).”). Following Prochaska and DiClemente [74], a six-choice response format is applied to categorize participants into the six different stages of change (e.g., 1 = *No, and I do not intend to start doing so within the next 6 months* for the precontemplation stage).

#### Social relationships

Social support is measured with the 11-item *Actually received social support* subscale of the Berlin Social Support Scales (BSSS [52];), a frequently used measure of different cognitive and behavioral aspects of social support. Respondents rate on a 4-point Likert scale how much emotional, instrumental, and informational social support they have received by their partners during the past weeks (e.g., “My partner encouraged me not to give up.”; *strongly disagree* (= 1) to *strongly agree* (= 4)). The scale’s internal consistency was Cronbach’s α = .83 in the original validation study [52].

Relationship connectedness describes the degree of belonging and relatedness between a person and their partner [75] and is measured using the item “How closely connected do you feel today with your partner?” [45]. Response categories range from 1 (*not close at all*) to 5 (*very close*) on a 5-point Likert scale.

#### Momentary self-control strength

Momentarily available self-control strength is measured by a German short version (SSCCS-K-D [62];) of the State Self-Control Capacity Scale (SSCCS [76];). Its 10 Items (e.g., “I feel sharp and focused.”) are rated on a 7-point Likert scale ranging from *not true at all* (= 1) to *very true* (= 7). In the validation study, Cronbach’s α was .87 [62].

#### Health-related quality of life

Health-related quality of life is measured using the German version [77] of the Short Form-8 Health Survey (SF-8 [78];), which is an abbreviated version of the original SF-36 Health Survey (SF-36 [61];), a generic instrument to measure perceived health status. The SF-8 measures eight domains (response categories) with one item each, including general health (1 = *excellent*, 6 = *very poor*), physical functioning (1 = *not at all*, 5 = *could not do physical activities*), role physical (1 = *none at all*, 5 = *could not do daily work*), bodily pain (1 = *none*, 6 = *very severe*), vitality (1 = *very much*, 5 = *none*), social functioning (1 = *not at all*, 5 = *not do social activities*), mental health (1 = *not at all*, 5 = *extremely*), and role emotional (1 = *not at all*, 5 = *could not do daily activities*). Using a norm-based scoring method [78], Physical Component Summary (PCS) and Mental Component Summary (MCS) measures can be calculated by weighting each item, with higher summary PCS and MCS scores indicating better health.

#### Sociodemographic information and dieting history

Information on sex and age are collected as self-reports at all three measurement points. Dieting history is assessed using the following three items [9]: (a) “Are you currently dieting (e.g., eating less than usual, eating only specific foods, skipping meals, fasting …)? ” – *yes* or *no*; (b) “Have you ever dieted?” – *yes* or *no*; (c) if the answer to the previous item is yes: “How often?” – *number of diets*. Based on these items, participants can be classified into three dieting groups (never, former dieters, current dieters).

#### Anthropometric information

Information on body height and body weight is collected online as self-reports at all three measurement points. In addition, study assistants measure the participants’ height and weight with calibrated instruments (a stadiometer by Seca and a MS 4202 medical floor scale by Marsden) in the laboratory. Participants are weighed and measured in light clothing and without shoes.

#### Heart rate variability

Heart rate variability (i.e., the variation in time between consecutive heartbeats) is considered a biological marker of self-regulation [79]. To assess heart rate variability at rest, an electrocardiogram (ECG) is recorded using the HRV scanner from BioSign GmbH, with clamp electrodes placed at both wrists (sampling rate of 500 Hz, 16-bit resolution). Participants are instructed to sit quietly in a comfortable, semi-upright position for 5 minutes and breathe normally. Pre-processing of data and score calculation will be performed with Kubios HRV software (version 3.5) [80]. The standard deviation of normal-to-normal RR intervals (SDNN) as a commonly used time-domain HRV index [65] will be calculated to quantify the amount of HRV between successive heartbeats.

#### Additional group-specific measures

T1_online_ and T2_online_ surveys comprise additional group-specific items that are used to measure intervention-related factors, such as subjective training success (“Overall, do you feel that your ability to perceive hunger and satiety signals has improved because of the training?”; 1 = *not at all*, 6 = *very much*) and recommendation of training (“Would you recommend the training to others?”; 1 = *not at all*, 6 = *absolutely)*.

### Intervention evaluation and acceptance

To assess participants’ overall acceptance of the training, its feasibility as well as its medium-term impact and (non-) continuation in everyday life, a two-step evaluative strategy consisting of training evaluation sheets as well as focus group discussions will be executed.

#### Training evaluation sheets

Intervention group participants are instructed to complete three self-constructed paper-pencil training evaluation sheets. Participants receive three largely identical questionnaires (one for each exercise) that are to be completed after each week of the training (see Fig. 3). Questionnaires comprise 19 items as well as 3 additional group-specific items for group 1 participants. Items assess different subjective evaluative aspects of the three exercises, such as comprehensibility, feasibility, user-friendliness, implementation into everyday life, and perceived barriers. All items are rated either on 5-point Likert scales or in an open-ended response format.

#### Focus group discussions

To explore participants’ acceptance of each exercise as well as their overall experiences across time, four qualitative focus group discussions [81] will be conducted at least 3 months after the follow-up measures. For the four qualitative focus group discussions (see Fig. 2), approximately *n* = 16–24 participants are drawn from the total sample (*N* = 60 couples). To allow for comparative qualitative analyses, two groups will ideally involve couples, and the others are planned with individuals who have completed the training either alone or together with their partner. The latter two groups are to be conducted separated by gender to allow for potential gender-related effects.

A semi-structured guideline will be developed to stimulate discussion and support the exchange of experiences among participants. This guideline will be informed by first descriptive results of the above-mentioned training evaluation sheets. The focus of the guideline lies on the overall intervention as well as specific experiences with the three training exercises (body scan mediation, hunger meditation, satiety meditation) over the course of time and within the couple context. For example, questions will address the influence and support of the partner in the implementation of the exercises. In addition, the guiding questions are aimed at the general potential for change in connection with intuitive eating, e.g., the extent to which everyday practices have changed by the time of the focus groups. The guideline will be adjusted according to the group composition (couples vs. individuals).

The focus groups will be recorded and the audiotapes will be transcribed. Each group discussion takes place at the German Institute of Human Nutrition Potsdam-Rehbruecke. Index persons are contacted via phone to clarify their readiness to participate. In case of agreement, participants receive detailed study information via email. Prior to the group discussions, each participant provides written informed consent – including consent for being audiotaped. Participation is compensated with an expense allowance of €20 per person.

### Data management and monitoring

Data of all online questionnaires (T0_online_, T1_online_, T2_online_) will be collected electronically using the secure online software SoSci Survey [51]. Data of all laboratory assessments (T0_lab_, T1_lab_, T2_lab_) will be entered electronically by the trained study assistants, using the Study Management System (SMS) of the HSZ. Data of the paper-pencil training evaluation sheets will be transferred to an electronic database by experienced data entry personnel via the online software SoSci Survey. All research data will be stored on a secure, password-protected computer server that will only be accessible to the research team. Range checks for all data values will be carried out to promote data quality. Web-based data collection and adherence to a detailed study manual within the laboratory assessments ensure standardization of data collection and thus further promote the quality of all research data.

Due to the health-promoting focus and preventive approach of the present study, no negative side effects are expected. Therefore, no stopping rules are defined. Moreover, no interim analyses are intended.

### Analyses

#### Hypothesis testing

Data will be analyzed using the per-protocol (PP) analysis. The study encompasses three measurement points, of which two are post-intervention. First, descriptive analyses will be performed to describe the baseline demographic characteristics, stratified by intervention group. Correlational patterns will be analyzed and requirements for statistical analyses will be checked. Our main analyses will be performed using Bayesian methods of inference. Following Wagenmakers and colleagues [82], Bayesian inference entails several advantages (such as its application to all sample sizes) compared to classical inference and thus represents a beneficial alternative to classical approaches. Using the Bayes factor, evidence for the alternative hypothesis (H_1_) is compared with the evidence for the null hypothesis (H_0_). Thereby, evidence for both hypotheses (H_1_ and H_0_) can be quantified from the observed data, which is another advantage of Bayesian inference compared to classical approaches [82]. If necessary, our analyses will be corroborated by classical null hypothesis significance testing using *p* values.

In order to investigate whether the training improved interoceptive sensitivity and intuitive eating and decreased maladaptive eating behaviors of the index persons from pre-intervention to follow-up, repeated measurements analyses will be performed for each construct of interest using multivariate linear regression models to determine intergroup effects, adjusting for the baseline values of the respective outcome variables. To analyze the training effect on interoceptive sensitivity (primary outcome), intervention group participants (group 1 and group 2) will be compared to control group participants (group 3) in terms of their MAIA scores as well as their interoceptive accuracy scores (HBPT) and WTL-II scores. Intervention group participants and their spouses will be compared to control group participants and their spouses in terms of their IES-2 and DEBQ subscale scores in order to analyze the training effect on different eating behaviors (secondary outcome). To test whether targeting couples enhances the effectiveness of the training, participants completing the training together with their spouses (group 1) will be compared to participants performing the training alone (group 2) and control group participants (group 3). Furthermore, correlative patterns between additional variables and outcome variables will be analyzed to be able to add relevant variables to the models. Also, exploratory analyses on the role of spouses within this intervention will be carried out.

Missing data per measurement point and over time are handled by full information maximum likelihood estimation (FIML [83];), a model-based statistical approach for handling missing data that produces unbiased parameter estimates and standard errors if data are missing at random. Studies have shown that FIML outperforms traditional approaches for handling missing data and performs as well as multiple imputation [84]. The analyses will be conducted using IBM SPSS Statistics 27, Mplus 7 [85], and JASP [86].

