### Participants and sample size

A total of *N* = 60 couples aged 50–80 years is to be recruited as a first test of the training feasibility and effectiveness. Eligible for inclusion are heterosexual couples who are living together and willing to participate in a randomized controlled trial. Since the intervention focuses on the promotion of intuitive eating behavior, participants with comparatively lower levels of intuitive eating have a high priority for invitation to participate in the randomized controlled trial (see next paragraph). Exclusion criteria include kidney diseases, gastrointestinal diseases, cognitive impairments, and cardiovascular problems (especially wearing a cardiac pacemaker).

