### Intervention groups and control group

Couples are randomly assigned to one of the two intervention arms (groups and 2) or a control group (group 3). Both intervention groups only differ with respect to how they implement the training in everyday life: Index persons of group 1 are instructed to complete the training with their partners. No further instructions are given regarding the exact implementation of training together. Index persons of group 2 are instructed to complete the training by themselves, i.e., without their partner. Participants of the control group (group 3) do not complete any training. However, after finalizing the follow-up measures, the control group is given the opportunity to receive the training as well.

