### Training in both intervention groups

The training consists of three different mindfulness-based audio exercises (body scan mediation, hunger meditation, satiety meditation), which participants are asked to perform daily over a period of 21 days. All exercises are provided as guided meditation audio files. In line with common recommendations [30], participants are asked to complete the exercises in a quiet place and avoid possible distractors (e.g., mobile phone, radio, television). Exercises should serve as a timeout from the daily routine, eyes should be closed during the exercises, upcoming thoughts or experiences should not be judged or criticized. Participants decide on their own at what time of day they want to practice. Participants are instructed to perform each exercise on seven consecutive days. All audiotapes include a short introduction followed by the specific exercise sequence and a short wake-up phase.

The first exercise (week 1) is a body scan meditation edited from a script by Kabat-Zinn and Valentin [47], based on the procedure described by Fischer and colleagues [30]. During this 20-minute exercise, participants are asked to lie down and focus their attention on different parts of the body, starting with the feet and moving up slowly to the top of the head. There is evidence that interoception can be improved by interventions that are based on body scan meditation [30]. Both the second and the third exercise are based on the intuitive eating woorkbook by Tribole and Resch [48]. During the second week, participants are instructed to perform a hunger meditation *before* a meal. During this 8-minute exercise, participants are first asked to sit comfortably. Subsequently, they are instructed to mindfully focus on the perception of hunger signals, such as their location and intensity as well as the type of sensation. The third exercise (week 3) is a satiety mediation that participants are asked to perform *after* a meal and, again, in a comfortable sitting position. During this 9-minute exercise, participants are instructed to focus on the perception of satiety signals, evaluate the extent of their satiety, and notice whether and how they feel satiety in their stomach or other body parts. A training schedule is presented in Fig. 3.

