Following the review of Schuman-Olivier et al. [49], the main skills/strategies that are targeted by the training are self-related processes (interoceptive awareness, self-efficacy, self-critical rumination and self-monitoring). Furthermore, the training also includes aspects of emotion regulation (emotion differentiation, decentering) and attentional / cognitive control (volitional orienting, alerting, conflict monitoring and inhibitory control).

To evaluate participants’ adherence to instructions, the post-intervention online survey (T1_online_) contains an additional group-specific item that serves as a manipulation check (e.g., group 2: “Did you actually do the training alone during the last 21 days or did you ask for or receive support from your partner?”; 1 = *alone*; 2 = *with my partner*).

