### Group allocation, blinding, and confidentiality

Groups are allocated using ID numbers (between 1 and 75) that were randomly assigned to the three groups prior to recruitment via the online software Research Randomizer (version 4.0) [50]. ID numbers (and thus the respective group) are assigned to the participants in the order in which they are included in the study. The random assignment of numbers ensures that no conclusions can be drawn between ID numbers and groups.

All participants are blinded throughout the pre-intervention measurements, as these precede the distribution of the sealed folders that contain information about the participants’ group (see paragraph ‘study procedure’). Participants are instructed to maintain strict silence about their group allocation during the post-intervention and follow-up measurements. Study assistants are blinded during all laboratory assessments. To ensure unbiased ascertainment and analysis of outcomes, data collectors, data managers (research personnel handling data coding and cleaning) as well as data analysts are blinded.

To maintain participant confidentiality, all study-related information will be stored securely at the HSZ of the German Institute of Human Nutrition Potsdam-Rehbruecke. All records that contain names or other personal identifiers, such as informed consent forms, will be stored separately from study records identified by ID numbers. All databases will be secured with password-protected access systems.

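### Per-protocol is the only analysis set named for the between-arm hypotheses 1–3, so the comparison with control can lose the protection of randomisation

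*Protocol article*

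**What the plan says.** The protocol article, under Analyses, Hypothesis testing, opens with "Data will be analyzed using the per-protocol (PP) analysis". It names no intention-to-treat or other as-randomised set there or elsewhere. The same section adds "Our main analyses will be performed using Bayesian methods of inference", with classical tests as possible support, and for incomplete data "Missing data per measurement point and over time are handled by full information maximum likelihood estimation".

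What a trained participant is asked to follow is spread over three places:

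- Training in both intervention groups describes three audio exercises, "which participants are asked to perform daily over a period of 21 days".
- Intervention groups and control group has group 1 train with the partner and group 2 train alone, while group 3 does no training. For group 1 it adds "No further instructions are given regarding the exact implementation of training together".
- The post-intervention online survey "contains an additional group-specific item that serves as a manipulation check". The example given, for group 2, asks whether the training was done alone or with the partner.

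The article does not say how many sessions count as following the protocol. It also does not say whether the manipulation-check answer affects who is analysed.

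**The concern.** Aim of this study frames hypotheses 1–3 as differences between randomised groups: trained versus control for interoception and for eating behaviour, and couple training versus training alone. Randomisation makes such differences interpretable only while couples are compared as they were allocated. A per-protocol set selects on what people did afterwards.

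That selection cannot be even across arms as far as training is concerned, because controls have no training to omit. If people who drop the exercises are also those who would change less for other reasons, such as motivation or health, removing them flatters training.

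The contrast between groups 1 and 2 has its own weakness. Training together or alone is both what is randomised and what the manipulation check asks about. Excluding couples who did the opposite of their assignment would make the contrast depend partly on which couples prefer to do things jointly.

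**Working it through.** The plan gives no figure to reproduce: no effect size, SD, dropout or adherence rate is stated. The check is a reading of the text, followed by an illustration on assumed inputs.

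**Reading the sections together**

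1. Analysis set: per-protocol only (Hypothesis testing).
2. Claims tested in it: hypotheses 1–3, all between-arm (Aim of this study).
3. Training obligations: daily exercises for 21 days and a partner pattern in groups 1 and 2, none in group 3. Training-related exclusions can therefore arise only in groups 1 and 2.
4. Timing: the manipulation check is answered after training, so anything it decided would be decided after allocation.
5. FIML: it uses the available values of participants who are in the analysis set. It does not restore someone excluded from that set.

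**Inputs for the illustration**

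- Target of 60 couples (Participants and sample size: "couples aged 50–80 years is to be recruited as a first test of the training feasibility and effectiveness").
- The list has "ID numbers (between 1 and 75) that were randomly assigned to the three groups prior to recruitment", with no ratio stated. Assuming 1:1:1, 60/3 = 20 couples per arm, so 40 trained and 20 control index persons.
- Excluded share p = 10–30%, scoring δ = 0.3–0.8 SD worse than those kept. Both are assumptions.

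**Shift of the trained-arm mean**

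Let m be the mean of those kept. The as-randomised mean is (1 − p)m + p(m − δ) = m − pδ, so the per-protocol mean is too high by pδ:

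- 0.10 × 0.3 = 0.03 SD
- 0.20 × 0.5 = 0.10 SD
- 0.30 × 0.8 = 0.24 SD

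This is the departure from the as-randomised mean. Where those excluded did worse because they trained less, part of it is a real dose effect. Baseline adjustment, which is planned, would remove any part of δ already visible in the baseline score.

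**A version with no true effect**

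Here training does nothing, the least adherent share q of trained participants is dropped, no control is dropped, and adherence is normal with correlation ρ to outcome change. The bias is ρ·φ(z_q)/(1 − q), in SD. Rejection is a two-sided 5% normal test with 40(1 − q) trained against 20 controls.

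| q | ρ | Bias (SD) | Rejection |
|---|---|---|---|
| 0.10 | 0.2 | 0.039 | 0.052 |
| 0.20 | 0.3 | 0.105 | 0.066 |
| 0.30 | 0.3 | 0.149 | 0.080 |
| 0.40 | 0.5 | 0.322 | 0.186 |

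The second row agrees with the simple formula: 0.105/0.20 gives an implied δ of about 0.53 SD.

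**Group 1 versus group 2**

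Equal p and δ in both groups cancel, so none of these figures measures bias in that contrast. What can be shown is loss of numbers. Excluding 20% from each group takes 20 to 16 per arm, and power of a two-sided 5% test for an assumed d = 0.8 falls from 0.72 to 0.62.

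**The case against.** The strongest reply is that one sentence is being made to carry too much. Several stronger readings are tempting, and the article does not support them.

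- **That couples who train too little, or with the wrong partner pattern, are dropped.** No section ties a session count or the manipulation check to exclusion. The definition of the set may sit in an analysis plan not shown.
- **That the control arm keeps everyone.** Controls have surveys, three laboratory visits and a two-hour restriction on eating and drinking before the water load test, and can deviate on these. Only training-related exclusions are confined to the trained arms.
- **That the whole study is analysed per protocol.** Research question 4, on acceptance and feasibility, is evaluated separately with evaluation sheets and focus groups.
- **That FIML contradicts per-protocol.** FIML can be applied within any analysis set.
- **That FIML cannot serve a Bayes-factor analysis, so the two plans clash.** How missing values enter the Bayesian model is detail an article may leave to the analysis plan.
- **That the result is biased upward by a known amount.** The inputs are assumed. With 40 versus 20, the standard error is √(1/40 + 1/20) = 0.27 SD, larger than every shift from 0.03 to 0.24 SD.

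It can also be said that this is a pilot offering first insights, and that the effect in those who actually train is a legitimate question.

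All six limits stand. The choice of set remains: it is stated, not left open, and it serves claims that the article itself calls effectiveness. Neither pilot status nor Bayesian inference repairs post-allocation selection, since a Bayes factor weighs whichever data are kept.

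**Conclusion.** The point holds as a fault in a stated choice. Per-protocol is the sole named set for hypotheses 1–3, and training-related exclusions can fall only on groups 1 and 2. Any such exclusion would take the comparison with control outside the protection of randomisation, probably in favour of training. For group 1 versus group 2 the threat is conditional on couples being excluded for their partner pattern, and its direction is unknown.

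The size cannot be obtained from the article. The 0.03–0.24 SD shift applies to trained versus control only, before baseline adjustment, and rests on assumed shares and gaps. Under no true effect, the middle case raises rejection only from 0.05 to 0.066; the figure of 0.186 needs the most extreme inputs tried. The case for change therefore rests on the loss of the randomised comparison, not on a demonstrated large bias.

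**What to change.** In Hypothesis testing, make the main analysis of hypotheses 1–3 include all randomised couples in their assigned arm, using every observed T0, T1 and T2 value whatever the adherence or the manipulation-check answer. The planned FIML handling can then apply to that full set. Keep per-protocol as a labelled sensitivity analysis, with its membership rule written down before the data are analysed, including whether and how the manipulation check counts.

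No new data collection is needed, because surveys and laboratory visits are already scheduled in all three arms regardless of adherence. The cost is a change of wording, one extra analysis run, and an estimated effect that may be somewhat smaller.
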